#### Clinic/medical data

Quantitative data will be collected from medical records and PĒPI ARC clinic notes and through communication with local and regional health professionals. Data will include demographic and ethnicity information, indication for entry into the CPCN Recommendations pathway, and completion of assessments including timing and results, diagnostic outcomes, and referrals for monitoring and interventions.

Descriptive statistics will be used to report participant characteristics, recruitment rates, attendance rate in clinics, completion of diagnostic tools, referral for early intervention, and surveillance (Objectives 1, 2, 4, and 5, Table 4). Analysis of Likert scale data from family, health professional, and PĒPI ARC team questionnaires will also be analysed using descriptive statistics (Objective 3, Table 4). If data are determined to be normally distributed, then continuous data results will be reported using means and standard deviations, or if data are not normally distributed, then median and interquartile ranges will be reported (lower and upper quartiles). Pearson's chi-squared or Fisher's exact test will be used to compare the extent of implementation of the best practice guidelines between regions and ethnicities. A *p* value of <0.05 will be considered statistically significant.

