### Primary objective

1.**Implementation:** to determine to what extent the CPCN Recommendations for early CP diagnosis can be equitably implemented for infants with newborn detectable risks who are admitted to a level 3 NICU (independent of place of residence and ethnicity) and if the fidelity of the CPCN Recommendations can be maintained

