### Hypotheses

**H1**: Equivalent levels of infants who meet the criteria will undergo assessments with CP-specific diagnostic tools outlined in the CPCN Recommendations, independent of region of residence or ethnicity.

**H2**: Whānau and health professionals will find the PĒPI ARC Hub model of care acceptable (over the acceptability constructs).

**H3**: The demand will be high with infants who meet the criteria choosing to enroll in the PĒPI ARC study over standard care.

**H4**: More than 34% of infants with CP will be diagnosed before 12 months of corrected gestation age (CGA) and >17% before the age of 6 months CGA.

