### Study design and setting

The PĒPI ARC study is a prospective, non-randomised, feasibility study that uses a mixed methods approach to evaluate the previously outlined domains of feasibility. The study will run from March 2023 to September 2024, with the primary time point being at the completion of the PĒPI ARC Hub trial period. The study setting will be a regional Hub based in Wellington to allow follow-up of eligible infants who received care at the Wellington NICU. The PĒPI ARC Hub will be delivered using two components: a community-based, multidisciplinary face-to-face diagnostic clinic in Wellington and a virtual Hub to support regional CP-specific neurodevelopmental follow-up, education, and information sharing and foster relationships among the Wellington team, local community, and regional child development services (CDS) and paediatricians.

The Wellington NICU is a tertiary unit that provides perinatal and surgical care for infants from Wellington and seven regional referral centres from half of the North Island and the top of the South Island of NZ. The unit cares for a third of all infants admitted to a tertiary NICU in NZ. It is estimated that between 100 and 120 infants per year will fit the criteria for the CPCN Recommendations pathway, of which approximately 30% live in the Wellington area (21) (i.e., to be invited to attend the in-person clinic), and the remainder will receive follow-up in their local regions (supported by the PĒPI ARC team through telehealth).

For the Wellington NICU catchment area, data from the NZ CP Register (2009–2020) showed that 17% of infants received a diagnosis of CP before 6 months of age and 34% before 12 months (22).

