### Participants and recruitment

Participants for this study will be formed by two groups, namely, the infants and their parent/caregivers, and the health professionals involved/interacting with the PĒPI ARC Hub. There are no limits placed on the sample size, and a formal sample size calculation is not required. Based on the historical figures of the number of infants admitted to the NICU at the Wellington Regional Hospital and infants aged <28 weeks, up to 120 infants are anticipated to meet the study eligibility during the 12-month recruitment period. There will be no restrictions on other care or interventions partaken in by participants.

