### Outcome measures and data collection

Feasibility will be assessed by using the outcomes, measures, and data capture summarised in Table 4, from March 2023 to September 2024. Data will be directly entered into REDCap (hosted by the Wellington Hospital and MRINZ infrastructures), which will only be accessed by the members of the research team involved in the data entry and analysis. Due to the scope and minimal risks associated with the study, there is no formal data monitoring committee. Interim data monitoring will be conducted at a 6-month review of survey feedback, and auditing of trial conduct will be completed by the primary investigator and study and clinical coordinators on a fortnightly basis. Quantitative data collection tools, surveys for families, health professionals and the PĒPI ARC MDT team, participant information, consent form, and data management plan are available on Open Science Framework (OSF, DOI: https://doi.org/10.1101/2023.10.31.23297869).

**Table 4 T4:** Summary of outcomes, data capture, and measures/approaches for PĒPI ARC.

Objective	Data capture	Measures/approaches
Implementation		
1. To determine to what extent the early CP detection assessments can be implemented equitably to infants with newborn detectable risks admitted to a level 3 NICU	• Demographic information for infants eligible for the CPCN Recommendations pathway (NICU discharge data) • PĒPI ARC clinic notes and medical records	The proportion of infants completing the neuroimaging, GMA, and HINE (as per CPCN Recommendations), with outcomes grouped and compared by: • Region of residence • Ethnicity (Māori, Pasifika, non- Māori/Pasifika)

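### Equity is asked about place and ethnicity together, but completion is compared by each factor alone, so an ethnic gap cannot be located and one confined to regional Māori infants is diluted

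*Protocol article*

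**What the plan says.** The Primary objective asks how far the early-detection recommendations can be implemented equitably, "independent of place of residence and ethnicity". Hypothesis H1 repeats this for completion of the diagnostic assessments: "independent of region of residence or ethnicity".

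Table 4, Objective 1, takes the proportion of infants completing neuroimaging, GMA and HINE, "with outcomes grouped and compared by" two listed factors: region of residence, and ethnicity in three groups (Māori, Pasifika, and neither). The section Clinic/medical data gives the analysis: "Pearson's chi-squared or Fisher's exact test will be used to compare the extent of implementation of the best practice guidelines between regions and ethnicities", with a p "value of <0.05 will be considered statistically significant".

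Place largely decides how the Hub is delivered. Under Study design and setting, about 30% of eligible infants live in the Wellington area and are to be invited to the in-person clinic; the rest are followed locally with telehealth support. Usual care also varies by place: three regional centres have GMA-trained clinicians and three more send videos to Wellington.

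**The concern.** The question involves two factors that may be linked, and each is examined without the other. Two consequences follow.

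- **Location of a gap.** If regions differ in completion and in ethnic mix, crude completion differs by ethnicity even when infants of all ethnicities in the same place are assessed equally. The crude comparison detects that difference but does not say where it comes from. One explanation points to delivery of the virtual Hub, the other to access within each site, and they call for different service changes.
- **Dilution.** If only regional Māori infants are under-assessed, each one-way table averages them with unaffected infants. A null region comparison could then be read as regional equity.

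A completion gap by place is foreseeable from the article itself. The Discussion accepts that some regional centres may lack experienced staff.

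**Working it through.** **Inputs from the article.** Study design and setting gives 100 to 120 eligible infants per year. Over the 12-month recruitment period this is 100 to 120, which agrees with "up to 120 infants are anticipated to meet the study eligibility during the 12-month recruitment period". At 30% in Wellington: 0.30 × 120 = 36 Wellington, 84 regional. No power or effect size is stated, so there is no further figure to reproduce.

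**Assumptions.** The article gives neither the ethnic mix by region nor expected completion, so both are varied. Ethnicity is reduced to Māori v other, and place to Wellington v regional, unless stated. Rejection rates are simulated (40,000 runs per setting, 5% level), with Pearson's test for crude comparisons and the Cochran-Mantel-Haenszel (CMH) test for stratified ones.

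**A. Purely regional gap, no ethnic difference within place.** Example: Māori share 20% Wellington, 50% regional (7 of 36; 42 of 84); completion 90% v 70%.

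- Other infants: (29 × 0.90 + 42 × 0.70) / 71 = 55.5 / 71 = 78.2%
- Māori infants: (7 × 0.90 + 42 × 0.70) / 49 = 35.7 / 49 = 72.9%

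The crude ethnic gap is 5.3 points, all of it arising through place.

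| Māori share, Wellington / regional | Completion, Wellington / regional | Crude ethnicity test rejects | Stratified by place rejects |
|---|---|---|---|
| 30% / 30% | 90% / 70% | 4-5% | 5% |
| 20% / 35% | 90% / 70% | 7% | 5% |
| 20% / 35% | 90% / 60% | 8% | 5% |
| 20% / 50% | 90% / 70% | 10% | 5% |
| 20% / 50% | 95% / 65% | 16% | 5% |
| 15% / 50% | 90% / 50% | 28% | 5% |

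With eight regions and three ethnic groups, closer to Table 4, and a Māori share of about 19% / 42%, the crude ethnicity test rejects in 6-7%.

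**B. Gap only in regional Māori infants.** Māori share 30% in both places (11 of 36; 25 of 84); completion 65% in regional Māori infants, 90% in all others.

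- Regional: (59 × 0.90 + 25 × 0.65) / 84 = 69.35 / 84 = 82.6%, against 90% in Wellington: gap 7.4 points, power 16%
- Māori: (11 × 0.90 + 25 × 0.65) / 36 = 26.15 / 36 = 72.6%, against 90% in others: gap 17.4 points, power 67%
- Within regional infants: 90% − 65% = 25 points, power 78%

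With eight regions and three ethnic groups, power is 9.5% by region and 60% by ethnicity. At 60% v 85% in the two-group layout it is about 13% by region, 58% by ethnicity and 70% within regional infants.

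**C. Which added contrast is safe.** Comparing regional Māori infants with everyone else has higher power in B (about 76% at 60% v 85%), but it mixes place with ethnicity. In the example under A, regional Māori infants complete 70%, and all others (36 × 0.90 + 42 × 0.70) / 78 = 61.8 / 78 = 79.2%. That is a 9.2-point gap with no ethnic difference within place. Across the unequal-mix settings tried, this contrast rejects in 15% to about 51% of runs. The contrast within regional infants stays at about 5%.

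**The case against.** **The crude rejections are not errors.** A reader might take the 7-28% in the table as false positives. The article does not support that. H1 is a marginal statement: if Māori infants live more often where completion is lower, fewer of them are assessed, and rejecting is right. Stratifying by place answers a different question, namely whether a gap remains among infants in the same place. This stands, so the crude comparison must stay.

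**The article may simply be silent.** A reader might infer that the plan rules out any stratified analysis. It does not; the sentence is condensed, and a fuller protocol or analysis plan may hold more. However, the article does fix the comparison for its primary objective, and that comparison takes one factor at a time, so improving it is a fair point.

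**The size is assumed.** This also stands. No ethnic mix by region is given, and the larger figures need a marked imbalance.

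**Stratified tests do not cure dilution.** Correct. At 60% v 85% in setting B, the ethnicity test has about 58% power whether crude or stratified, and the region test about 14% either way. The contrast within regional infants is what recovers the gap. Two strata may also be too coarse: where completion and Māori share were assumed to vary across the seven regions, with no ethnic effect within any of them, the two-stratum test still rejected in 9-13% of runs, against 15-20% for the crude test.

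**Other parts of the study help.** Interview sampling is checked for regional and ethnic spread, and the themes are meant to inform the quantitative data. Wellington families who cannot attend are offered telehealth, so place and delivery are not perfectly tied. Interviews may suggest why a gap exists, but they do not measure completion by place and ethnicity.

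**Conclusion.** The concern holds in a limited form. The stated comparisons can show a marginal gap by region or by ethnicity. They cannot show whether an ethnic gap arises through place or within it, and they weaken a gap confined to regional Māori infants: strongly by region (25 points to 7.4) and mildly by ethnicity (25 to 17.4) in the worked case. Those figures assume 120 infants, a 30% Māori share in both places, and 65% v 90% completion.

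The difference between crude and stratified ethnicity results depends on the unknown ethnic mix. It vanishes with an equal mix and is modest at moderate imbalance. The 120 is also an upper figure for eligible infants; families may choose usual care, so the number analysed may be smaller. This is a low-cost improvement to a feasibility study, not a flaw that invalidates its primary comparison.

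**What to change.** In Clinic/medical data and in Table 4, Objective 1:

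1. Keep the crude comparisons by region and by ethnicity.
2. Add completion of each assessment by place (Wellington v regional) crossed with ethnicity, with counts and 95% confidence intervals.
3. Report the ethnicity comparison stratified by place (CMH or an exact stratified version, with finer region strata where numbers allow) beside the crude one, so that a crude inequity is not explained away.
4. Prespecify the ethnicity contrast within regional infants. Do not use regional Māori and Pasifika infants v all others, which is itself confounded by place.
5. State that the added results are read as estimates with intervals, not as further tests at 5%.

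The cost is a few lines of analysis text, since residence, ethnicity and completion are already collected. The downside is small cells and wide intervals, especially for Pasifika and Wellington Māori infants; the latter cell may hold only 4 to 14 infants under the mixes considered. A formal interaction test would have about 34% power in the 65% v 90% case, so it should not be relied on.

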### Study aim, objectives, and hypotheses

This study aims to evaluate the feasibility of equitable implementation of a pathway for the early detection of CP for infants with newborn detectable risks (criteria outlined in Table 1) who are admitted to a tertiary NICU in NZ through a multidisciplinary regional Hub called the PĒPI ARC Hub. Based on the work of Bowen et al. (17), (i) **implementation**, (ii) **acceptability (**18), (iii) **demand,** and (iv) **limited efficacy** of PĒPI ARC will be studied.

**Table 1 T1:** Criteria for infants within the newborn detectable risks, as outlined in the New Zealand CPCN best practice recommendations for early detection of cerebral palsy (CP), intervention, and monitoring (CPCN recommendations).

Newborn detectable risk criteria
1. Any infant born <28 + 0 weeks gestation. OR 2. Any infant born ≥28 + 0 weeks gestation with one or more detectable risk factors for CP: i. Weight < 1,000 g ii. Intrauterine growth restriction Birth weight <3rd percentile on population-based or customised growth charts or at clinician's discretion based on concern about pathological growth restriction. iii. Abnormal findings on neuroimaging associated with CP [e.g., Grade 3 and 4 intraventricular haemorrhage, post-haemorrhagic ventricular dilatation, hydrocephalus, periventricular leukomalacia (PVL), stroke, brain maldevelopment]. iv. Hypoxic ischaemic encephalopathy (HIE)—Grade 2 and 3. v. Neonatal encephalopathy of other aetiology. vi. Neonatal meningitis/ encephalitis—bacterial or viral. vii. Cardiac surgery viii. Clinical or parental concerns or other significant risk factors—clinician discretion.

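### The infant-level chi-squared and Fisher tests of equity do not allow for multiple births, which modestly raises the chance of declaring inequity

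*Protocol article*

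**What the plan says.** - **Hypothesis.** H1 (Protocol article, Hypotheses) covers both where the family lives and its ethnic group. It opens with "Equivalent levels of infants who meet the criteria will undergo assessments with CP-specific diagnostic tools outlined in the CPCN Recommendations, independent of region of". It belongs to the primary objective.
- **Unit and grouping.** Table 4, Objective 1 gives the measure as "The proportion of infants completing the neuroimaging, GMA, and HINE (as per CPCN Recommendations), with outcomes grouped and compared by" two factors. The first is where the family lives; the second is listed as "Ethnicity (Māori, Pasifika, non- Māori/Pasifika". The unit is the infant.
- **Test.** Under Clinic/medical data, the tests named are Fisher's and Pearson's chi-squared. The sentence ends with "exact test will be used to compare the extent of implementation of the best practice guidelines between regions and ethnicities". The threshold is stated next: a p "value of <0.05 will be considered statistically significant". No rule for choosing between the two tests is given.
- **Population.** Table 1 begins with "Any infant born <28 + 0 weeks gestation" and adds, from 28 weeks on, low weight, growth restriction and other infant-level risks. The eligibility criteria under Infants and parents/caregivers place each infant by discharge address. They neither exclude multiples nor limit entry to one infant per family.
- **Size.** Under Participants and recruitment, "up to 120 infants are anticipated to meet the study eligibility during the 12-month recruitment period".

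Twins, triplets, siblings and clustering are not mentioned anywhere in the article. Some demand measures in Table 4 are counted by family, but the equity measure is counted by infant.

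**The concern.** Chi-squared and Fisher's exact test treat each infant as a separate piece of evidence. Siblings from one birth go home to one address, so they always fall in the same region group, and they normally share an ethnic group. Several determinants of completion act on the whole family: whether it takes part, whether it films and sends the movement videos after discharge, and whether it can attend a clinic or needs telehealth. If siblings tend to complete or miss assessments together, the completion proportion in each group varies more than the test assumes, and p values come out too small.

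At stake is the only inferential comparison that the article names, and it serves the primary objective. Because H1 predicts equivalent levels, p values that are too small lead to reporting a regional or ethnic gap that is not there. In a small group, a few non-completing sibling sets could be enough to do this.

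**Working it through.** The article states no power, effect size or margin, so there is no figure of its own to reproduce. The check asks how far the real type I error can lie from 5%.

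**Inputs from the article.** Up to 120 infants; about 30% live in Wellington (Study design and setting), which gives 0.30 × 120 = 36 against 84; alpha 0.05, taken as two-sided because the article does not say.

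**Inputs assumed, because the article gives none.** Share of infants who are twins, f = 10-30%; sibling correlation in completion, ICC = 0.3-1.0; completion 60-90%.

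**Formulas.** With siblings always in the same group, the design effect for twins is DEFF = 1 + f × ICC. The actual two-sided error of the unadjusted test is 2 × [1 − Φ(1.96/√DEFF)]. The effective number of infants is 120/DEFF.

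| f | ICC | DEFF | Effective N | True SE / assumed SE | Actual alpha |
|---|---|---|---|---|---|
| 0 | any | 1.00 | 120 | 1.000 | 5.0% |
| 10% | 0.3 | 1.03 | 116.5 | 1.015 | 5.4% |
| 20% | 0.5 | 1.10 | 109.1 | 1.049 | 6.2% |
| 25% | 0.8 | 1.20 | 100.0 | 1.095 | 7.4% |
| 30% | 1.0 | 1.30 | 92.3 | 1.140 | 8.6% |

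Triplets act in the same way. With 20% twins and 5% triplets, DEFF = 1 + (0.20 × 1 + 0.05 × 2) × ICC, which is 1.15 at ICC 0.5 (6.8%) and 1.30 at ICC 1 (8.6%).

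**Simulation.** 20,000 trials of 36 against 84 infants with no true difference; chi-squared without continuity correction. Each cell gives the chi-squared error / the Fisher error.

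| Twins, ICC | 60% completion | 80% completion | 90% completion |
|---|---|---|---|
| none | 5.3% / 4.2% | 4.7% / 3.5% | 5.1% / 3.1% |
| 20%, 0.5 | 6.6% / 5.4% | 6.1% / 4.6% | 6.2% / 3.7% |
| 20%, 0.9 | 7.4% / 5.8% | 7.4% / 5.9% | 7.6% / 4.7% |
| 30%, 0.5 | 7.1% / 5.7% | 6.8% / 5.2% | 6.5% / 3.9% |
| 30%, 0.9 | 8.7% / 7.2% | 8.6% / 6.6% | 8.5% / 5.3% |

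For three ethnic groups (sizes assumed as 36, 14 and 70; 80% completion), the chi-squared error is 4.8% with no twins, 6.1% at 20% twins with ICC 0.5, and 8.6% at 30% twins with ICC 0.9.

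**Which test would be used?** If the choice followed the common rule of an expected count of at least 5 (an assumption), the smallest expected count for 36 against 84 is 36 × 0.20 = 7.2 at 80% completion, which points to chi-squared. At 90% it is 36 × 0.10 = 3.6, which points to Fisher. If the seven referral centres are kept separate, they average 84/7 = 12 infants, or 12 × 0.20 = 2.4 expected non-completers each at 80% completion, which again points to Fisher.

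**The case against.** - **Silence in a condensed article.** The article never says that siblings are treated as independent, and a full protocol or analysis plan that is not shown may deal with clustering. This stands in part: silence on multiples alone would be no finding. But the article commits to named tests on an infant-level outcome, and a later plan would have to change or qualify those tests, not merely add detail.
- **Infant-level drivers.** A reader might infer that siblings are almost perfectly correlated because they would be seen together. The article does not support this. No section says that siblings share an appointment. From 28 weeks on, Table 1 lets one twin qualify without the other. The usual-care section says that early movement assessments can be missed because of the infant's own condition, and that MRI is routine only for the two higher encephalopathy grades. In Table 2, referral for MRI depends on that infant's own results. This stands, and it is why the correlation is shown as a range.
- **Fisher's conservatism.** A reader might infer that the primary analysis certainly exceeds 5%. It does not if Fisher's test is used and completion is high: the simulated error is 3.7-5.3% with twins at 90% completion. This also stands, although the article allows chi-squared, which has no such cushion.
- **Intervals.** A reader might infer that confidence intervals would be too narrow. The article plans none for this comparison, so that reading has no basis.
- **Small consequence.** This is a feasibility study without a sample size calculation and with mainly descriptive reporting. Too-small p values cannot create a false claim of equity. This stands, and it limits the weight of the point.

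**Conclusion.** The concern holds as a minor point. The article fixes an infant-level outcome and tests that require independent infants, while its eligibility rules admit siblings who share the grouping factors. On assumed twin shares of 10-30% and correlations of 0.3-1.0, the chi-squared error is about 5.4-8.6%, centrally about 6-7% (20-25% twins, ICC 0.5-0.8 gives 6.2-7.4%). Fisher's test lies at about 3.5-6.6% at 80% completion. The size rests wholly on those assumptions; if no multiples enrol, the problem disappears. The direction does not depend on their exact values: any positive sibling correlation pushes towards declaring inequity too often.

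**What to change.** 1. Record a family identifier for each infant, if the database does not already hold one, and report the number of multiple-birth sets by region and ethnic group.
2. Keep the infant as the unit of description, but test the region and ethnicity differences with a permutation test that moves whole families between groups. Where cells are not sparse, a Rao-Scott chi-squared or a GEE clustered on mother would also serve.
3. As a minimum, keep the named tests and add a sensitivity analysis with one infant per family.

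The cost is one data field and a few lines of analysis text, with no change to recruitment or care. P values become slightly larger. Robust-variance methods are unreliable in sparse cells, which is why the permutation test is the first choice for small regional or ethnic groups.
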